### Study population

Participants will be women who are newly diagnosed with GDM and plan to deliver their baby at a tertiary hospital in Western Australia, where all study visits and routine antenatal care will be undertaken. Inclusion criteria include women diagnosed with GDM through a routine 75 g Oral Glucose Tolerance Test (OGTT) between 24 and 30 weeks of pregnancy and ≥ 18 years of age. A diagnosis of GDM is made using the International Association of Diabetes in Pregnancy Study Groups (IADPSG) diagnostic criteria of one or more values reaching the following levels – Fasting glucose ≥5.1 mmol/L, 1-h ≥ 10.0 mmol/L, 2-h ≥ 8.5 mmol/L [41].

Participants will be excluded if they have an early diagnosis of GDM before 24 weeks; Overt Diabetes in Pregnancy; Type 1 Diabetes; T2DM; poorly controlled hypothyroidism; Graves’ Disease; twin pregnancy; breastfeeding; vegetarian; vegan; irritable bowel syndrome; inflammatory bowel disease; previous bariatric surgery; history of an eating disorder; allergy to adhesives; antibiotic use in the past 3 months; use of steroids, antipsychotics, metformin, laxatives, fibre supplements or probiotic supplement; any major medical disorder; any psychosocial issues likely to impact on ability to adhere to study protocol.

Demographic information will be collected from the digital medical record (DMR) and participants will complete a demographic questionnaire at Baseline to obtain information on ethnicity, medical and obstetric history, medication and dietary supplement usage.

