### Primary outcome

#### Fasting blood glucose

The primary outcome of this study will be a reduction in median FBG from Baseline, within and between groups. Baseline FBG will be recorded from the diagnostic OGTT results [41]. Subsequent venous blood samples will be collected after an overnight fast at Day 10 and Day 56 and analysed for FBG following protocols from the National Association of Testing Laboratories. FBG within treatment targets (< 5.1 mmol/L) [49] is the measure of glycaemic control that has been most difficult to achieve with standard GDM diet and lifestyle interventions and therefore the variable most likely to indicate the need for medical therapy, such as insulin [50]. If FBGL below 5.1 mmol/L is not achieved by Day 10, insulin therapy will commence. Participants treated with insulin will remain in the study.

Routinely women will receive self-monitoring of blood glucose (SMBG) education. Participants will be provided with an SMBG meter and instructed on measuring blood glucose levels four times daily (FBG and 2-h post-prandially). The SMBG meters used will be either Contour Next (Ascensia Diabetes Care, Switzerland), Accu-Chek Guide (Roche Diabetes Care, Switzerland) or One Touch Verio (LifeScan, USA) and meet International Organization for Standardization (ISO) standards for accuracy. Data from these models will be uploaded via the Diasend Uploader (Glooko, USA). FBG will be monitored on the first 2 days and averaged to provide a Baseline measure. This will be compared to the moving averages over the subsequent 8 days of testing, and then again between Days 48 and 56, across the three dietary groups (Control, RS Diet and RS Supp) using mixed model ANOVA with group-by-time interaction.

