### Statistical analyses

Baseline demographic and outcome variables will be described and compared for differences between groups. Continuous variables will be described as mean ± standard deviation (SD) and nominal and ordinal variables as frequencies and proportions. All continuous variables will be examined for normality using the Shapiro-Wilk test. Descriptive statistics for non-normal continuous variables will be presented as median ± interquartile range (IQR).

FBG and PPBG will be monitored on the first 2 days and averaged to provide a Baseline measure of each outcome. These will be compared to those measured over the subsequent 8 days, and then again between Days 48 and 56, across the three dietary groups (Control, RS Diet and RS Supp) using linear mixed modelling with group-by-time interaction. Analysis will assess if a 0.3 mmol/L reduction is achieved. Demographic variables such as age, pre-pregnancy BMI, parity and ethnicity will be adjusted in the model. Statistical analyses will be performed using SPSS® (Statistical Package for Social Sciences, version 27 for Windows).

The number of PPBG excursions experienced by a participant per day between Days 4 to 10 will be examined and compared relative to the number determined at their Baseline over the first 2 days of the usual care diet. Generalised Mixed Modelling will be utilised to assess whether a dietary change reduces the frequency of PPBG excursions as compared with norm with adjustments for relevant demographic variables.

Different R packages and PRIMER 7 (Quest Research, NZ), a non-parametric statistical software package, will be used to assess change within and between groups for microbial composition. Distance Based Linear Modelling (DistLM) will be used to look for a correlation between change in stool microbiota or SCFA & measures of glycaemia.

Direct and indirect costs savings related to any reduction in insulin treatment or improvements in maternal and neonatal outcomes will be calculated from DRG codes, Weighted Activity Units (WAU) and the National Efficient Price (NEP) and reported [74].

Missing data will be treated in statistical analysis as missing and coded as 999 or left blank, so as not to affect the accuracy of the analysis. Prior to any statistical analysis, all data will be explored for outliers. Any outliers found will be cross-checked with the source file. Any true outliers will be checked with the clinician before being removed/left in the dataset.

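### The primary outcome includes within-arm falls from the diagnostic fasting value and gives 0.3 mmol/L no comparator; the planned between-group test is valid but less precise than a baseline-adjusted one

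*Protocol article*

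**What the plan says.** Under Primary outcome, Fasting blood glucose, the protocol article states: "The primary outcome of this study will be a reduction in median FBG from Baseline, within and between groups". For the venous measure, "Baseline FBG will be recorded from the diagnostic OGTT results"; the later venous samples are at Day 10 and Day 56. Under Study population, a woman enters when that same test shows "one or more values reaching the following levels". The fasting threshold is 5.1 mmol/L, but the 1-h or 2-h value alone is enough.

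The Statistical analyses section uses another Baseline: "FBG and PPBG will be monitored on the first 2 days and averaged to provide a Baseline measure of each outcome". The later readings are compared across the three groups "using linear mixed modelling with group-by-time interaction". It then adds: "Analysis will assess if a 0.3 mmol/L reduction is achieved". It does not say whether this is a fall within an arm or a difference from Control. The covariates named are age, pre-pregnancy BMI, parity and ethnicity, given as examples; baseline fasting glucose is not among them.

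The Background hypothesis is comparative, against standard dietary advice. The Sample size section powers a within-between interaction and sets 0.3 mmol/L beside a 0.4 mmol/L difference seen between control and supplemented groups.

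**The concern.** Three features of the wording combine badly.

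- **Within-group change is part of the primary outcome.** Nothing says which component governs or that the within-group part is descriptive.
- **The 0.3 mmol/L mark has no comparator.** It can be read as a fall from Baseline in one arm.
- **The venous Baseline is a value on which many women were selected.** Those who qualified on fasting glucose will on average be lower at retest without any treatment effect. All arms also receive standard dietary advice, and insulin may start in any arm after Day 10. Falls that Control also shows are therefore to be expected.

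At stake is a report in which a resistant starch arm appears to meet the primary outcome through a fall that Control shows too. Separately, a small trial gives up precision by not using a baseline measurement that it already collects.

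**Working it through.** **1. The plan's own figure.** d = 0.3/0.86 = 0.349, so f = d/2 = 0.174, stated as 0.175. For the within-between interaction with 3 groups and 3 times, λ = f²·N·m/(1−r). With r = 0.5 (assumed; the article gives no correlation), λ = 0.175² × 69 × 3/0.5 = 12.68 on 4 and 132 degrees of freedom. Power is 81.1%, and 69 is the smallest multiple of three that reaches 80%. The stated 69 is reproduced (96 at r = 0.3, 42 at r = 0.7). The trial is thus powered on a between-group contrast of changes.

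**2. Regression to the mean in women selected on fasting glucose.** Expected fall = (1−r)·s·φ(z)/(1−Φ(z)), with z = (5.1−m)/s. The threshold 5.1 is from Study population. The screened mean m (4.5–4.8), SD s (0.4–0.6) and retest correlation r (0.5–0.8) are assumptions.

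| m | s | r = 0.5 | r = 0.7 | r = 0.8 |
|---|---|---|---|---|
| 4.5 | 0.5 | 0.42 | 0.25 | 0.17 |
| 4.6 | 0.5 | 0.38 | 0.23 | 0.15 |
| 4.8 | 0.4 | 0.27 | 0.16 | 0.11 |
| 4.8 | 0.6 | 0.34 | 0.21 | 0.14 |

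Example: m = 4.6, s = 0.5 gives z = 1.0 and φ/(1−Φ) = 1.525. At r = 0.7 the fall is 0.3 × 0.5 × 1.525 = 0.23. The range is roughly 0.1 to 0.4, reaching 0.46 only at the corner m = 4.5, s = 0.6, r = 0.5.

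A rough average for a whole arm uses the article's mean of 5.175: (1−r)(5.175−m) runs from 0.2 × 0.375 = 0.08 to 0.5 × 0.675 = 0.34.

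**3. What a shared fall does.** Simulation with no diet effect, 30 per arm, SD 0.86, r = 0.5, 4,000 runs per setting:

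| Fall common to all arms | One given RS arm falls ≥0.3 | At least one RS arm falls ≥0.3 | At least one RS arm has a significant within-arm fall |
|---|---|---|---|
| 0.2 | 26% | 44% | 41% |
| 0.3 | 49% | 75% | 71% |

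Check on the first cell: the SE of an arm's mean change is 0.86 × √(2×0.5)/√30 = 0.157, and 1−Φ(0.1/0.157) = 26%.

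The group-by-time interaction rejected in 4.4–5.3% of runs for common falls from 0 to 0.3, against a nominal 5%.

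**4. Precision.** The variance of a change score is 2σ²(1−r); after baseline adjustment it is σ²(1−r²). The ratio is (1+r)/2 = 0.65, 0.75, 0.85 at r = 0.3, 0.5, 0.7. Pairwise power for 0.3 mmol/L at one follow-up time, 30 per arm, SD 0.86, two-sided 5%, normal approximation:

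| r | Change score | Baseline-adjusted |
|---|---|---|
| 0.3 | 21% | 29% |
| 0.5 | 27% | 35% |
| 0.7 | 42% | 47% |

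At r = 0.5 the standard errors are 0.86 × √(2/30) = 0.222 and 0.86 × √0.75 × √(2/30) = 0.192. The t distribution gives values up to about one percentage point lower. These are single pairwise contrasts, not the omnibus test of step 1, and serve only to size the gain.

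**The case against.** The strongest reply is that the efficacy test is between groups. The hypothesis, the stated design aim, the sample size and both descriptions of the mixed model are comparative. A fall common to randomised arms cancels in the interaction, and the simulation confirms this. This stands. A reader might infer that success is judged by within-group falls; the article nowhere says that a within-arm fall alone decides efficacy.

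Second, the 0.3 mmol/L sentence follows the two-day monitored Baseline, which is measured after diagnosis and is not the selecting value. This also stands. The regression argument applies to the venous outcome and is weaker for the monitored one. It is weaker again for women who entered on the 1-h or 2-h value. With the article's mean and SD, and assuming normality, about 47% of women lie below 5.1: Φ((5.1−5.175)/0.86) = 0.47.

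Third, a reader might take the 0.3 sentence as a rule that the point estimate must reach 0.3, which a true effect of exactly 0.3 would meet only half the time. The article states no such rule. The fair criticism is the missing comparator.

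Fourth, omitting baseline as a covariate costs precision and does not bias the test. The covariate list is open, and detail may sit in an analysis plan not shown. That limits this part to an efficiency gain. The power figures also depend on the SD: at SD 0.5 and r = 0.5 they are 63% and 75% (t distribution).

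None of this removes the within-group element from the primary outcome or supplies the comparator.

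**Conclusion.** The point holds as a defect of definition together with an available gain in precision. The primary outcome contains a component that cannot test the hypothesis, and the 0.3 mmol/L mark can be read within an arm. On that reading, regression to the mean of roughly 0.1 to 0.4 mmol/L among women selected on fasting glucose could account for much or all of the target. The size depends on the assumed screened-population mean, SD and retest correlation, and is smaller across a whole arm. The planned interaction test is not invalidated.

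Baseline adjustment would lower the variance of the contrast by 15–35% and add about 5 to 8 percentage points of pairwise power at SD 0.86, for assumed correlations of 0.3 to 0.7. The article also gives two Baseline definitions for fasting glucose, so it is unclear which one the 0.3 mmol/L mark refers to.

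**What to change.** - State that the primary inference is the between-group difference in fasting glucose versus Control. Remove the within-group element from the primary outcome and report arm changes descriptively.
- Express 0.3 mmol/L as that between-group difference. Use it as a relevance mark beside the estimate and its 95% confidence interval, with the test made against zero.
- Fit the mixed model to Day 10 and Day 56 with baseline fasting glucose by time as a covariate, or keep Baseline as an outcome and constrain its mean to be equal across arms.
- Reconcile the Baseline definitions in the Primary outcome and Statistical analyses sections, saying which measurement serves the primary analysis.

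The cost is protocol or analysis-plan wording and model syntax. Baseline fasting glucose is already collected, so no extra visit, sample or participant is needed.

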### Secondary outcomes

#### Post-prandial glucose

Post-prandial blood glucose (PPBG) will be measured by participants using SMBG three times per day for three consecutive days. The change in mean 2-h PPBG and frequency of PPBG levels above the target for each mealtime will be calculated and compared within and between groups at Baseline (Day 1–3), Days 8–10 and Days 54–56. Two-hour PPBG excursions of 6.7 mmol/L or more are considered above the target for optimal pregnancy outcomes [49]. Elevated PPBG are associated with preeclampsia, caesarean section delivery, large for gestational age (LGA), neonatal hypoglycaemia [6] and childhood glucose and IR [10].

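### Post-prandial excursions are analysed as a number per day with no denominator of readings taken, so the count can fall simply because fewer meals were tested

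*Protocol article*

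**What the plan says.** Statistical analyses (protocol article) sets the follow-up measure as "The number of PPBG excursions experienced by a participant per day between Days 4 to 10 will be examined", to be "compared relative to the number determined at their Baseline over the first 2 days of the usual care diet". The model is given in general terms: "Generalised Mixed Modelling will be utilised to assess whether a dietary change reduces the frequency of PPBG excursions", with demographic adjustment. No distribution, link or offset is named, and neither is the number of readings taken. The same section says that missing data are treated as missing, coded 999 or left blank.

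The readings come from self-monitoring. Under Fasting blood glucose, "Participants will be provided with an SMBG meter and instructed on measuring blood glucose levels four times daily", meaning one fasting and three post-prandial tests. Under Post-prandial glucose, the tests are made "three times per day for three consecutive days" per window, and an excursion is a 2-h value of 6.7 mmol/L or more.

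Post-prandial glucose also states the outcome in another form: "frequency of PPBG levels above the target for each mealtime will be calculated and compared within and between groups". Its windows are Days 1–3, 8–10 and 54–56, whereas the excursion analysis uses the first 2 days and Days 4–10.

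**The concern.** A daily count has an implied denominator of three tested meals. When a woman tests only two, the count for that day is still a valid number, but it comes from two opportunities. A low count may then mean good control or little testing.

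Two comparisons are exposed. The first is each woman against her own baseline, which is short: a few lost readings there would lower the baseline count and could hide a real fall. The second is between arms: if one arm tests less during Days 4–10, it shows fewer excursions whatever its glucose. The trial is open-label, and the supplement arm also keeps a supplement diary and makes fortnightly returns, so equal testing should be checked and not assumed.

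**Working it through.** The documents report no excursion rate and no testing completeness, so there is no figure of the plan to reproduce. What follows shows how the stated measure behaves.

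**Inputs from the protocol article.** Three planned post-prandial readings per day. A baseline of 2 days gives 3 × 2 = 6 readings; the 3-day baseline under Post-prandial glucose gives 3 × 3 = 9. Days 4–10 are 7 days, so 7 × 3 = 21 readings.

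**Assumptions.** The excursion risk p per meal is the same at all meals, readings are missed independently of glucose, and a missed reading adds nothing to the day's count.

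**Baseline.** With m of 6 readings lost, the expected count per day is p(6 − m)/2, against 3p with full testing. The understatement is m/6. With unchanged risk and complete follow-up, the apparent follow-up/baseline ratio is 6/(6 − m).

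| Lost of 6 | Understated | Apparent ratio, no true change |
|---|---|---|
| 0 | 0% | 1.00 |
| 1 | 16.7% | 1.20 |
| 2 | 33.3% | 1.50 |
| 3 | 50.0% | 2.00 |

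On a 9-reading baseline, 1 or 2 lost gives 1/9 = 11.1% or 2/9 = 22.2%. If every arm loses the same share, the factor cancels in a between-arm ratio: for one lost reading, 1.20/1.20 = 1.

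**Between arms at follow-up.** With completeness c, the expected count per day is 3pc, so the false rate ratio is c(RS)/c(control).

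| Control | RS | False rate ratio |
|---|---|---|
| 90% | 90% | 1.00 |
| 95% | 90% | 0.947 |
| 95% | 85% | 0.895 |
| 85% | 95% | 1.118 |

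**Effect on the test.** Two simple simulations used 95% against 85% completeness, no diet effect, 21 planned readings, mean risk of about 0.25 and a two-sided 5% t-test between two arms. With 23 women per arm and Beta(2.5, 7.5) risks (3,000 runs), the count per day rejected in 7.9% of runs and excursions per reading in 5.2%. With 30 per arm and a between-woman SD of 0.5 on the logit scale (4,000 runs), the figures were 12.1% and 4.6%. At 90% in both arms, the second set-up gave about 4% for either measure. These runs show the pattern; they are not the planned mixed model.

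**With readings as denominator.** The expected value is p at any completeness, so both distortions vanish under the missed-at-random assumption.

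**The case against.** The strongest reply is that the article never says an untested meal is scored as free of excursion, and that its general rule keeps missing data missing. The model is only named as a generalised mixed model. A reading-level binomial model or an offset would both fit that name, and such detail is often left to an analysis plan. This is fair, and a reader who infers that the plan scores blanks as zero goes beyond the text. The missing-data rule does not settle the matter, however. A day with two of three readings has a non-missing count. If incomplete days were instead set to missing, one partly tested day would remove half of a 2-day baseline. The text chooses neither, and the outcome it does state is a number per day.

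A reader might also infer that the baseline is in fact understated by 17–33%, because women are enrolled at a clinic visit on Day 1. The documents do not support this. They give no time at which the meter is issued, and the first 2 days may run from the Day 1 visit to the Day 3 visit, when self-monitoring data are collected, with nothing lost. The fasting baseline, also an average over those 2 days, fits that reading better than a lost first morning.

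Nor do the documents show that testing will differ by arm. Self-monitoring is routine care for all women, the completeness figures above are assumed, and the direction is unknown: if RS women test more, the bias runs against the diet.

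**Conclusion.** The point holds in a limited form. The excursion outcome is written as a count per participant per day with no denominator of readings, so it can move with testing frequency as well as with glucose. No actual bias is demonstrated. The sizes above are conditional on assumed losses, and their range starts at zero. A shortfall at baseline affects within-woman change only, provided it is equal across arms; a false between-arm effect needs unequal testing at follow-up. Separately, the two sections describe the excursion measure and its windows differently and need to be reconciled. The outcome is secondary and the severity is minor; the case for change is that the better measure is nearly free.

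**What to change.** Replace the number per day with excursions per recorded 2-h PPBG reading. Either fit a binomial generalised mixed model at reading level with mealtime as a factor, or fit a count model with log(readings taken in the window) as offset. Use the same denominator at baseline and at follow-up. State which days form each window, and bring the paragraph into line with the per-mealtime frequency under Post-prandial glucose. Report readings taken out of those planned, by arm and window, so that a reader can see whether testing differed.

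The cost is one rewritten paragraph; the number of readings can be taken from the planned meter uploads. There are two small drawbacks: women with few readings carry less weight, and readings skipped because a high value was expected remain a source of bias that no denominator removes.

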### Intervention

#### Dietary intervention

All women will receive standard GDM dietary advice in line with evidence-based guidelines [2, 40, 43, 44]. Women will be encouraged to consume a minimum carbohydrate intake of 175 g per day, from mostly low glycaemic sources, distributed across the day over three meals and three snacks. The dietary advice will promote a low saturated fat intake and higher consumption of vegetables, fruit, dairy and whole grains.

After Baseline data are collected, women who are randomised to either of the two dietary intervention groups (RS Diet & RS Supp) will receive additional dietary education on consuming a high RS diet commencing on Day 3. All RS dietary education will be conducted by the PI who is an experienced Accredited Practising Dietitian (APD). A standardised teaching plan (Supplement 3) and education materials will be utilised (Supplements 4 & 5). Participants will be provided with written material including a Gut Feeling cookbook [45] and sample menus, as well as some non-perishable samples of high RS foods to allow for immediate adoption of the diet. Dietary RS will be measured at Baseline, Day 10 and Day 56 using 3-day weighed food records (Supplement 6). Evidence of compliance with the high RS diet will also be monitored via urine samples for metabolomic analysis and change in stool microbiota at the same timepoints. Participants will be asked to continue the high RS diet until the delivery of their child.

The RS education tools and strategies have been piloted in a non-pregnant population and achieved a median increase in dietary RS intake of ≥6.6 g RS per day (unpublished data). The typical intake of RS in Australian women aged 19–44 years has been estimated to range from 2.9–8.3 g per day [46]. Similarly, recent data from the United States estimated the mean daily intake of RS to be 1.9 g per 1000 kcal for women of this age [47], which would equate to 3.8–5.7 g per day.

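### Both post-prandial glucose endpoints have conflicting day windows: Day 3 is baseline in one section but not in another, and the promised late excursion comparison has no model

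*Protocol article*

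**What the plan says.** Secondary outcomes, Post-prandial glucose: PPBG is self-monitored "using SMBG three times per day for three consecutive days". Two endpoints are drawn from it: "The change in mean 2-h PPBG and frequency of PPBG levels above the target for each mealtime will be calculated". Both are "compared within and between groups at Baseline (Day 1–3), Days 8–10 and Days 54–56".

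Statistical analyses, linear mixed model: "FBG and PPBG will be monitored on the first 2 days and averaged to provide a Baseline measure of each outcome". The follow-up periods are then given: "These will be compared to those measured over the subsequent 8 days, and then again between Days 48 and 56". Counting on from Days 1–2, the 8 days are Days 3–10.

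Statistical analyses, generalised mixed model: the outcome is "The number of PPBG excursions experienced by a participant per day between Days 4 to 10", set against the first two days, which the text describes as days on usual care. No later period is named.

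Two other sections bear on Day 3. Dietary intervention says that women in the two RS groups "will receive additional dietary education on consuming a high RS diet commencing on Day 3". Overview of study design places Baseline at Days 1–3.

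**The concern.** These windows are not left open for a later document to fill. They are fixed twice, differently, and no section says which governs. An analysis plan written afterwards could not satisfy both sections.

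Three things are at stake. First, Day 3 changes sides. If the RS groups already show some effect that day, counting it as baseline takes part of the effect out of the change from baseline. Second, Statistical analyses says that the modelling will assess whether a 0.3 mmol/L reduction is achieved, and the choice of days can move an estimate across that mark. Third, the late excursion comparison is listed among the secondary outcomes, but the only excursion model described stops at Day 10.

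The early period is where the definitions differ most. Because insulin is decided at Day 10, it is also the comparison least affected by insulin. The trial is open-label, so it is better that the governing windows are fixed before anyone sees the data.

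**Working it through.** There is no stated figure to reproduce, so the check is a count of days followed by an illustration of what the counts can do.

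**Step 1. Days and scheduled readings per woman** (inclusive days × 3 post-prandial readings per day).

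| Endpoint | Section | Baseline | Early | Late |
|---|---|---|---|---|
| Mean PPBG | Post-prandial glucose | Days 1–3: 3 d, 9 | Days 8–10: 3 d, 9 | Days 54–56: 3 d, 9 |
| Mean PPBG | Statistical analyses, linear mixed model | Days 1–2: 2 d, 6 | Days 3–10: 8 d, 24 | Days 48–56: 9 d, 27 |
| Excursions | Post-prandial glucose | Days 1–3: 3 d, 9 | Days 8–10: 3 d, 9 | Days 54–56: 3 d, 9 |
| Excursions | Statistical analyses, generalised mixed model | Days 1–2: 2 d, 6 | Days 4–10: 7 d, 21 | none |

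Day 3 is baseline in rows 1 and 3, follow-up in row 2, and in neither period in row 4.

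**Step 2. Share of the full effect recovered.** Let e(d) be the fraction of the full effect present on day d in an RS group, with e = 0 on Days 1–2.

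Share = mean of e(d) over the follow-up days − mean of e(d) over the baseline days.

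This treats each window as one pooled average. For excursions it applies to the daily rate on an additive scale. The protocol gives no time course, so the four below are assumptions.

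Early comparison:

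| Assumed time course | Post-prandial glucose windows (both endpoints) | Linear mixed model (mean PPBG) | Excursion model |
|---|---|---|---|
| Full from Day 3 | 1 − 1/3 = 0.67 | 1.00 | 1.00 |
| Full from Day 4 | 1.00 | 7/8 = 0.875 | 1.00 |
| Half on Days 3–4, then full | 1 − 0.5/3 = 0.83 | (0.5 + 0.5 + 6)/8 = 0.875 | (0.5 + 6)/7 = 0.93 |
| Linear, 0 on Day 3 to full on Day 10 | (5 + 6 + 7)/(7 × 3) = 0.86 | 28/(7 × 8) = 0.50 | 28/(7 × 7) = 0.57 |

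Late comparison: the Post-prandial glucose windows recover 0.67, 1.00, 0.83 and 1.00 in the same order. The linear mixed model windows recover 1.00 in all four cases. The excursion model has no late estimate.

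**Step 3. In mmol/L, for mean PPBG.** Take a true effect of 0.30. If it is full from Day 3, the early estimates are 0.30 × 0.67 = 0.20 and 0.30 × 1.00 = 0.30. Under the linear rise they are 0.30 × 0.86 = 0.26 and 0.30 × 0.50 = 0.15. Neither set of windows is favoured in every case.

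**Step 4. Precision.** If one woman's readings are independent, the standard error of her follow-up mean on 9 readings exceeds that on 21, 24 or 27 by √(21/9) = 1.53, √(24/9) = 1.63 or √(27/9) = 1.73. For baseline, moving from 9 to 6 readings gives √(9/6) = 1.22. These ratios concern within-woman error only.

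**The case against.** The strongest defence is that Day 3 is a changeover day. RS education follows baseline collection, so some Day 3 readings may precede it. Days 1–3, 8–10 and 54–56 are also the food-record days, so the Post-prandial glucose section may describe a summary matched to diet. Both are plausible, but the text says neither. A day that is partly pre-intervention needs explicit placement all the more.

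A second defence is that a mixed model with a group-by-time term need not pool Days 3–10 into one mean, and daily terms would not dilute the effect in this way. That stands as a limit on Step 2. It does not reconcile the day ranges.

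Some stronger readings are tempting but not supported:

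- A reader might see three estimands for one outcome. There are two endpoints, each with two conflicting definitions. The two models in Statistical analyses serve different endpoints and share the Days 1–2 baseline.
- A reader might conclude that no Day 56 excursion result is planned. The Post-prandial glucose section does promise one; what is missing is a matching model.
- A reader might attribute a fixed dilution to the two-day supplement introduction. That requires zero effect before Day 5. The introduction applies only to RS Supp, at a reduced amount rather than none, and no step-up is described for RS Diet. On that assumption Day 3 would not contaminate baseline either.
- A reader might extend the point to self-monitored fasting glucose. The Fasting blood glucose and Statistical analyses sections agree on those windows.
- Choosing a window after seeing the data is a possibility that the text leaves open. Nothing shows that it is intended.

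**Conclusion.** The contradiction is on the page and holds for both PPBG endpoints: Post-prandial glucose against the linear mixed model for mean PPBG, and against the generalised mixed model for excursions. The late excursion comparison is promised without a model. Day 3 has three different roles.

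The numerical effect is conditional: the same data can give different effects, not must. Under the assumed time courses, the early share for mean PPBG is 0.67 against 1.00 if the effect is immediate, 0.83 against 0.875 if half is present on Days 3–4, and 0.86 against 0.50 if it rises slowly. The wide gaps need either an immediate effect or a slow rise. All these figures assume pooled windows.

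The point should be corrected before analysis, but its reach is limited. PPBG is a secondary outcome, and the venous fasting glucose primary outcome is not affected.

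**What to change.** State one governing set of windows for each PPBG endpoint, in the same terms under Post-prandial glucose and Statistical analyses.

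- **Baseline:** use Days 1–2 for PPBG, which Statistical analyses already treats as usual-care days. Say explicitly whether Day 3 is follow-up or unused. State that this differs from the general Days 1–3 Baseline in Overview of study design.
- **Follow-up:** choose one early and one late window per endpoint from those already stated.
- **Excursions:** add the late window to the generalised mixed model with a group-by-window term. Model readings at or above the protocol's 6.7 mmol/L threshold out of readings recorded, so that windows of different length and missed readings are handled.
- **Sensitivity:** report the other stated windows as sensitivity analyses.
- **Unchanged:** leave the self-monitored fasting glucose windows as they are.

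The cost is small: revised wording and a little more analysis. No new measurement is needed, because the Fasting blood glucose section has women testing four times daily without restriction to 3-day blocks. The real trade-off is precision. If the 3-day follow-up windows are made primary, the within-woman standard error of the follow-up mean is about 53% to 73% larger than with the longer windows, assuming independent readings. Keeping the longer windows avoids that, but includes days when the effect may still be developing.
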